**Figure 3 F3:**
[figure not shown]
**Examples of two participant-selected tasks.** These photographs depict a participant engaged in two sensorimotor tasks, each addressing different motor impairments and movement skills. The study participant selected these two tasks during her ASAP sessions for practice.

#### Standardization for the ASAP protocol

To ensure data quality and consistent administration of the intervention among all ASAP therapists, a staged standardization process (Phase 1 and 2, Phase 3 and Re-certification) was developed. At each stage, an expert reviewer (experienced members of the ICARE Investigative team) assesses the digital video footage accompanying documentation for therapist mastery of each ASAP principle implemented during a 1 hr session. Phase 1 and 2 standardizations must be attained working with a volunteer with stroke before a therapist may initiate therapy with a randomized participant in the ICARE trial. Once Phase 1 and 2 standardizations have been attained, the therapist may begin working with an ASAP-randomized participant to complete Phase 3 standardization. After Phase 3 standardization is acquired, the therapist must re-certify according to the schedule directed by the reviewer. If in the worst case scenario, a therapist fails to demonstrate ASAP treatment fidelity at Phase 3 certification or recertification thereafter, all post-randomization data accrued for a participant seen by that therapist will be designated unusable for outcome analysis.

The Phase 1 and 2 standardization processes include demonstration of mastery in the following three task areas: 1) administration of the Brief Self-Efficacy Question; 2) determination of the challenge threshold and fundamental movement problem for two arm and hand activities, and 3) determination of appropriate task practice intensity and activity/task progression. Additional mastered elements for Phase 1 and 2 include: generalized ASAP protocol awareness via a knowledge test and therapist self-assessment of at least 90% mastery. Phase 3 standardization is attained via demonstrated mastery of the ASAP protocol through review of the 1^st^ and 20^th^ treatment sessions administered to the new therapist’s first ASAP randomized participant. Recertification is maintained through demonstration of continued mastery, on a target schedule of approximately every 6 months. During the trial start-up period, a 3-day training workshop was held for all ASAP therapists to attain Phase 1 standardization. Intervention therapists in all stages of standardization and the protocol developers facilitate ongoing training via monthly ASAP therapist teleconferences with video and literature review, individual conferencing, an on-line discussion board, and site visits for digital video review and discussion of ASAP principles and clinical experiences.

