### Type of design

ICARE is a parallel group, three arm, single blind, phase III, superiority, randomized, controlled trial of a principle-based upper extremity training program provided in the outpatient setting after the acute hospitalization phase. Once discharged from an inpatient or acute setting and following baseline assessment, participants are randomized, no earlier than 14 days and no later than 106 days after stroke onset, to one of three intervention groups: ASAP, DEUCC or UCC. The primary outcome, collected at 1 year post-randomization, is the log WMFT time score. The secondary outcomes are the SIS hand domain subscale and the full SIS scores. To prevent unintended crossover, details of the ASAP protocol are currently embargoed; therapists who provide ASAP sign a confidentiality and nondisclosure agreement and do not provide UCC or DEUCC treatments. Outcome assessors are blinded to treatment group. The study flow is illustrated in Figure 1.

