#### Analysis plan

This trial addresses two different questions separated by primary aim and secondary aim: 1) Is ASAP superior to DEUCC (primary aim)?, and 2) Is ASAP or DEUCC superior to UCC, (secondary aim) For all analyses, assumptions required for the data distribution (e.g., normal distribution) will be assessed. Any transformations of data or alternative methods necessary to analyze the data will be determined by examining the structure of the data. All analyses will be performed in accord with the intent-to-treat (ITT) principle (e.g., group status is determined by randomization at baseline). A p-value < 0.05 will be used to indicate statistical significance for all analyses.

The primary aim analyses will compare the ASAP and DEUCC group change in log WMFT time score and success rate from the SIS hand domain and the full SIS. For the primary hypothesis, change in WMFT time score at 1 year, an independent sample t-test will be used to compare the mean change in log-transformed WMFT time score, and analysis of covariance (ANCOVA) will be used to adjust for *a priori* covariates (site, initial motor impairment, stroke duration to randomization, baseline log time score) and any baseline variables that were imbalanced between ASAP and DEUCC. For missing data from loss to follow-up or missed evaluations at 12-months, multiple imputation using all available evaluation data will be utilized. Adjusted least-square means and the associated 95% confidence interval will be presented as well as p-value, and effect sizes will be computed to aid in interpretation of results.

For the secondary hypothesis, the success rate of the SIS hand domain will be calculated as the percent of subjects in the ASAP and DEUCC groups that achieved at least a 25-point increase in normalized SIS hand function at 1 year post randomization compared to baseline. Logistic regression will be used to compare these rates between groups, while adjusting for covariates. Since there are no prior data or biological evidence suggesting that ASAP will have a differential effect on one subgroup compared to DEUCC in the targeted population, we are not planning any *a priori* interactions between treatment and any of the covariates in the main analysis. However, we will perform exploratory data analysis to examine these possible interactions and generate hypotheses for future studies.

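### The rule voiding outcome data when an ASAP therapist fails fidelity review is a contingent, one-arm, post-randomization exclusion that conflicts with intention to treat whenever it is triggered

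*Protocol article*

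**What the plan says.** Under Standardization for the ASAP protocol, the article describes staged certification in which "an expert reviewer (experienced members of the ICARE Investigative team) assesses the digital video footage" and accompanying documentation for mastery of the ASAP principles. Phases 1 and 2 are completed with a volunteer before any trial participant is treated. Phase 3 uses trial participants: "Phase 3 standardization is attained via demonstrated mastery of the ASAP protocol through review of the" first and twentieth "treatment sessions administered to the new therapist’s first ASAP randomized participant". Recertification follows at a target interval of about six months.

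The consequence of failure is then stated. If, in what the article presents as a worst case, "a therapist fails to demonstrate ASAP treatment fidelity at Phase 3 certification or recertification thereafter", then "all post-randomization data accrued for a participant seen by that therapist will be designated unusable for outcome analysis".

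The Analysis plan section states: "All analyses will be performed in accord with the intent-to-treat (ITT) principle". The abstract also lists intention-to-treat analyses as a design feature. The same Analysis plan section specifies multiple imputation for loss to follow-up and for missed 12-month evaluations, and does not mention data designated unusable.

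Under Type of design, therapists who deliver ASAP "do not provide UCC or DEUCC treatments". The sections on UCC and DEUCC contain no fidelity-based exclusion of data.

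**The concern.** Certification status becomes known only after participants have been randomized and largely treated. Dropping participants on that basis from one arm breaks the comparability that randomization provides. Weakly delivered ASAP can leave the analysis while weakly delivered usual care always stays. The trial's primary question is whether ASAP beats the same number of hours of usual therapy. Under the rule, the estimate would move toward certified ASAP against all DEUCC.

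The reviewers belong to the investigative team and, because they are watching ASAP sessions, know the arm. Even if they judge with complete integrity, a rule that lets the trial's own team decide whose outcomes count in the experimental arm is hard to defend to an outside reader.

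**Working it through.** **1. Can both statements be followed?** With no therapist failure, yes. With a failure, the certification section makes an ASAP participant's outcomes unusable while the analysis section requires analysis as randomized. No sentence limits the first to a per-protocol or sensitivity analysis.

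**2. Does imputation resolve it?** The imputation rule names two causes: loss to follow-up and missed 12-month evaluations. An outcome that was collected and then voided is neither. The rule also voids all post-randomization data, so the post-intervention and 6-month evaluations would go too, leaving only baseline data for that person. The imputation model is not given. If it drew on retained ASAP participants, it could carry the same bias.

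**3. The plan's own figures.** Assume 120 per arm (360 in three equal arms; the ratio is not stated).
- 17% attrition: 120 × 0.83 = 99.6 per arm. The two-sided t-test at 0.05 with 80% power detects 0.399 (plan: 0.40).
- 25% attrition: 120 × 0.75 = 90 per arm, detecting 0.420 (plan: 0.42).

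Both reproduce. The sample size is not at fault.

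**4. Size of the shift.** Let f be the share of ASAP participants excluded and d the amount, in SD, by which their mean benefit falls short of the retained participants' mean. The intention-to-treat mean is (1 − f) × retained + f × (retained − d) = retained − f·d. Analysing only the retained participants therefore moves the ASAP–DEUCC difference by f × d toward ASAP.

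The documents give neither f nor d. I assume d = 0.25 to 0.75 SD and show several values of f:

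| Scenario | f | Shift, d = 0.25 to 0.75 | As % of 0.40 |
|---|---|---|---|
| No failure, or d = 0 | any | 0 | 0 |
| One participant removed | 1/120 = 0.0083 | 0.002 to 0.006 | 0.5 to 1.6 |
| One 6-month interval at one site | 2.6/120 = 0.021 | 0.005 to 0.016 | 1.3 to 4.0 |
| Whole caseload, 1 of 14 therapists | 1/14 = 0.071 | 0.018 to 0.054 | 4.5 to 13 |
| Whole caseload, 1 of 7 therapists | 1/7 = 0.143 | 0.036 to 0.107 | 9 to 27 |

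The number of therapists is not given; 7 and 14 are assumptions based on seven sites with trained back-ups.

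**5. How many would a failure touch?** Planned accrual is 3 per month at each of three centers, or 9 per month. With equal allocation and an even split over seven sites, that is 9 / 3 / 7 = 0.43 ASAP participants per site per month. At three sessions a week, session 20 falls at 20/3 = 6.7 weeks, about 1.5 months, by when 1.5 × 0.43 ≈ 0.7 further participants have joined. A Phase 3 failure would thus touch about 1 to 2 people. A six-month recertification interval holds 6 × 0.43 ≈ 2.6.

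**6. Effect on error rates** (normal approximation, 17% attrition, true intention-to-treat effect of zero). The chance of a false finding in favour of ASAP is 2.5% without a shift. It is 2.6 to 2.8% with one participant removed at d = 0.25 to 0.75, and 4.6% with 10% of the arm removed at d = 0.4. In the extreme case of f = 1/7 and d = 0.75 it is 10.9%. Power at 0.40, ignoring any shift, falls from 80.6% to 78.5% when 10% of the ASAP arm is removed.

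**The case against.** Several points on the other side are sound.

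- **The trigger is contingent.** The article treats failure as a worst case, and it may never happen. A reader might infer that the two statements can never both be followed; the text supports a conflict only when a failure occurs.
- **The direction is not established.** A reader might infer that the rule necessarily biases toward ASAP. Nothing shows that participants of a failing therapist do worse. Review concerns the therapist's mastery of ASAP principles, not the participant's response. If ASAP content added nothing over dose-matched usual care, poor adherence to it would not by itself worsen outcomes; some other cause, such as generally weaker therapists, would be needed. Bias toward ASAP is the expected direction, conditional on d > 0.
- **The upper figures are a ceiling.** They require a therapist's entire caseload to be voided. The sentence speaks of a participant in the singular, so its reach is unclear, and a Phase 3 failure would affect very few people. The seven-therapist case also supposes that the back-ups treat no one.
- **Intention to treat is glossed by group assignment.** One could keep participants in their randomized group and impute. That is a possible reading, but the gloss is given as an example, and discarding observed outcomes still gives up much of what intention to treat protects.

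A reader might also infer that reviewers would choose exclusions knowing the outcomes. The article does not say so.

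What stands is that the exclusion rule is written into the protocol without limit to a secondary analysis, applies to one arm, and operates after randomization.

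**Conclusion.** The point holds in a conditional form. The article authorizes a one-arm exclusion, decided after randomization by members of the investigative team, that conflicts with its intention-to-treat commitment whenever it is applied. It is liable to favour ASAP in the primary comparison if the excluded participants do worse.

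The size is unknown and may be nil. A single exclusion would be negligible, and the largest case shown depends on stacking the assumptions of seven therapists, a fully voided caseload and a 0.75 SD deficit. More than one failing therapist would add to it. The case for correction rests on the text rather than on these figures: a primary analysis should not contain a rule of this kind, and removing it costs almost nothing.

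**What to change.** Delete the sentence under Standardization for the ASAP protocol, or restrict it explicitly to a supportive fidelity (per-protocol) analysis. State in the Analysis plan that outcome data of all randomized participants are retained and analysed in the group assigned, and that a therapist's certification failure is recorded as a flag. Use the flag only in the supportive analysis, and define there which of the therapist's participants it covers.

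The Current study status section reports that an interim analysis was completed in November 2011 while enrollment was continuing. The article does not say whether any data had been voided by then. If any had, they should be restored for the final analysis, and the report should say whether the interim analysis excluded them.

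The cost is a short text change, carried into the manual of procedures and any separate analysis plan, plus a check for data already designated unusable. The planned power is unchanged. The downside is a slightly diluted ASAP estimate if a therapist does fail, which is part of what an effectiveness comparison is meant to reflect.

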#### Usual and customary care (UCC)

The UCC group receives Outpatient Occupational Therapy for the upper extremity as determined by each participant’s individual occupational therapist, based upon usual and customary practice standards. In accordance with those practices, the participant attends a standard Occupational Therapy evaluation session prior to initiating intervention sessions (treatment). The number of visits and frequency (dose) for the intervention is determined per the therapy prescription generated at the evaluation, site-specific usual and customary practices, and payer guidelines (e.g. private insurance, HMO, Medicare). The evaluation may have occurred prior to randomization. The dose may be modified per usual and customary practices as the intervention ensues. The treating therapist(s) documents each session per the treating facility’s protocol and documentation methods. The CSC of the clinic that randomized the participant is responsible for procuring the evaluation and treatment records and gleaning the necessary information for ICARE using standardized forms. Vital signs, as well as any symptoms of fatigue or stress are monitored during each session in accordance with usual and customary standard practice.

#### Dose-equivalent usual and customary care (DEUCC)

The DEUCC group initially receives Outpatient Occupational Therapy for the upper extremity as determined by each participant’s individual therapist, based upon usual and customary practice standards in a manner identical to the previously described UCC group with respect to content. Differentiating this group from UCC is its dose-equivalency with the ASAP group; each receives 30 hours of distributed treatment. Prior to initiating treatment (intervention) and in accordance with usual and customary practices, the participant receives a standard Occupational Therapy evaluation, where a recommended number of visits and frequency (dose) are determined, in accordance with site-specific usual care practices. This evaluation may have occurred prior to randomization. Immediately following the initial evaluation, the therapist and patient are notified of group assignment and 30 sessions are scheduled. According to protocol, if more than 30 treatment sessions are scheduled, the CSC will indicate that the treatment window is closed and a post-test will be scheduled. Provision of further treatment is documented via the monthly telephone interviews. Documentation and data are collected in a manner identical to that for the UCC group.

#### Dose of therapy (ASAP and DEUCC)

Thirty hours of training was chosen for the ASAP protocol because this dosage fell within the range of previous rehabilitation intervention trials that were shown to be effective in the post-acute outpatient setting. A training schedule of 30 hours of treatment, ideally distributed into 1 hour sessions, 3 days per week over 10 weeks is the anticipated experimental frequency for both the DEUCC and the ASAP groups. Both interventions vary in content and structure only. Pilot data from a multi-site outpatient survey conducted prior to initiating ICARE suggested that 30 hours of training would be higher than that commonly prescribed in the outpatient post-acute setting, and the 1 hour session length was designed to afford practicality and allow patients to participate in other concurrent therapy services (e.g., physical therapy and speech therapy). Those randomized to DEUCC or ASAP are expected to receive at least 90% (≥ 27 hours) of the 30 scheduled hours between 10 to 16 weeks post-randomization to be considered adherent to the dosing protocol. Therapy may extend up to 16 weeks to compensate for delays in initiating treatment post-randomization, missed sessions due to illness or other unavoidable absences. Precise tracking of therapy dose is maintained on all participants including: frequency and duration of individual treatment sessions, duration of total treatment sessions, and number of missed and canceled appointments. Additionally, for the UCC and DEUCC groups, initial OT prescription, prescription change, treatment venue and change in treatment venue are documented.

### Statistical analysis

#### Sample size and participant accrual

Sample size estimates were computed for the primary *a priori* aim of detecting a clinically relevant difference in log-transformed WMFT time score between ASAP and DEUCC at 1 year follow up with α = 0.05. With the proposed total sample of 360, we would have sufficient power to detect a moderate difference in treatment effect of Δ = 0.40 for an attrition rate of 17%, and Δ = 0.42 for an attrition rate of 25% using a two-group 2-sided t-test with a type I error of 0.05 and 80% power. The EXCITE trial showed treatment effect sizes of 0.50 and 0.63 for the high and low functioning groups, respectively. For the small sample phase II VECTORS study, a similar analysis showed a treatment effect size of 0.20. Given the outpatient timing of ICARE, a less dynamic period of change than VECTORS, we expect to have sufficient power to detect the effect size in log WMFT time score. We also should have sufficient power to detect a difference in the proportion of participants who change ≥ 25 points on the normalized SIS at 1 year using a χ^2^ statistic. The minimal success rate difference that can be detected with 80% power ranges from 13.5-20% (with 17% attrition) to 14.0-21% (with 25% attrition); the variation in the estimates reflects potential variation in improvement in the DEUCC group. To achieve this recruitment goal (N = 360) in 40 months, each of the three centers aims to randomize 3 participants per month.

### Specific aims

#### Primary Aim and hypotheses

##### Specific Aim 1

To compare the efficacy of a fully-defined, evidence-based and theoretically defensible therapy program (ASAP) and an equivalent dose of usual and customary Occupational Therapy (DEUCC) initiated within the earliest post-acute outpatient interval (14–106 days post stroke) for significant gains in the primary outcome of paretic upper extremity function 1 year after randomization.

##### Hypothesis 1

At 1 year post randomization, the time score from the WMFT will be significantly smaller (faster) after ASAP than usual and customary occupational therapy care (DEUCC), controlled for dose.

##### Secondary hypothesis for SA 1

At 1 year post randomization, the proportion of patients with successful outcomes measured by the Stroke Impact Scale (SIS) hand domain and full SIS will be greater after ASAP than DEUCC, controlled for dose.

#### Secondary Aim and hypotheses

##### Specific Aim 2A

To compare the efficacy of a fully-defined, evidence-based and theoretically defensible therapy program (ASAP) to that of an observation only usual and customary (UCC) occupational therapy program initiated within the earliest post acute outpatient interval (14–106 days post stroke) for significant gains in the primary outcome of paretic upper extremity function 1 year after randomization.

##### Hypothesis for SA 2

At 1 year post randomization, the time score from the WMFT will be significantly smaller (faster) after ASAP than UCC, uncontrolled for dose.

##### Secondary hypothesis for SA 2A

At 1 year post randomization, the proportion of patients with successful outcomes measured by the SIS hand and full SIS will be greater after ASAP than UCC, uncontrolled for dose.

##### Specific Aim 2B

To compare the efficacy of one dose-equivalent usual and customary outpatient occupational therapy program (DEUCC) to an observation only, usual and customary outpatient occupational therapy (UCC) program initiated within the earliest post-acute outpatient interval (14–106 days post stroke) for significant gains in the primary outcome of paretic upper extremity function 1 year after randomization.

##### Hypothesis for SA 2B

At 1 year post randomization, the time score from the WMFT will be significantly smaller (faster) after DEUCC than UCC, uncontrolled for dose.

##### Secondary hypothesis for SA 2B

At 1 year post randomization, the proportion of patients with successful outcomes measured by the SIS hand domain and full SIS will be greater after DEUCC than for UCC, uncontrolled for dose.

### Primary statistical analyses

#### Baseline

Descriptive statistics of demographics, baseline characteristics, and distributions will be performed for the total sample and for each group. Group comparisons will be made to examine whether any of these variables need to be accounted for in further analysis due to an imbalance across groups. Continuous variables will be compared using ANOVA for normally distributed variables to test for mean differences, and Wilcoxon rank sum test will be used for non-normally distributed variables to test for median differences. χ^2^ or Fisher’s exact test will be used for categorical variables to test for frequency differences. Participant characteristics that differ at baseline will be included as covariates in the analysis of the primary and secondary outcomes.

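### Beyond four pre-named covariates, the adjusted primary and secondary models take further covariates from tests of baseline imbalance, so they are not fixed in advance

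*Protocol article*

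**What the plan says.** Two places in the protocol article, both under Primary statistical analyses, govern covariate choice.

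- **Baseline.** Demographic and baseline variables are summarised overall and by group, then compared between groups to decide which of them later analyses must account for. The tests are ANOVA for normal variables, chi-square or Fisher's exact for categorical ones, and for the rest: "Wilcoxon rank sum test will be used for non-normally distributed variables to test for median differences". The section ends with a commitment: "Participant characteristics that differ at baseline will be included as covariates in the analysis of the primary and secondary outcomes".
- **Analysis plan.** The primary hypothesis gets an independent-sample t-test on change in log WMFT time and an ANCOVA. The ANCOVA has four a priori covariates: site, initial motor impairment, time from stroke to randomization, and baseline log time. It also takes in "any baseline variables that were imbalanced between ASAP and DEUCC". Adjusted means, a 95% confidence interval and a p-value are to be presented. The general significance level is 0.05, and the article gives no separate threshold for imbalance. The next paragraph carries the same approach to the comparisons with UCC.

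Participants are randomized "to one of three intervention groups: ASAP, DEUCC or UCC".

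**The concern.** With concealed, stratified randomization, any baseline difference between arms is a chance event. A small baseline p-value identifies an unusual draw, not a variable that predicts WMFT time at one year. A rule built on such p-values can admit variables with no bearing on outcome. It can also leave out useful predictors, beyond the four already fixed, because they happened to be balanced.

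At stake is the adjusted result. Its covariate list cannot be written down until the baseline data have been compared by arm, and the standard error takes no account of that step. The article assigns the interim and primary outcome analyses to an unblinded statistician, so a list that needs no judgement is worth having.

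The two places also leave open which comparison drives the selection. The Baseline section speaks of imbalance across groups after describing every group, and it names ANOVA, which suggests three arms. It also names a two-group rank-sum test without naming a pair. The Analysis plan refers to ASAP and DEUCC only.

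**Working it through.** **1. The plan's own figures.** Inputs from Sample size and participant accrual: "With the proposed total sample of 360", "using a two-group 2-sided t-test with a type I error of 0.05 and 80% power", "Δ = 0.40 for an attrition rate of 17" per cent and "Δ = 0.42 for an attrition rate of 25" per cent. Equal allocation (120 per arm) is assumed because the ratio is not stated. The detectable standardised difference is (1.960 + 0.842) × √(2/n).

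- 17% attrition: n = 120 × 0.83 = 99.6, taken as 99. The result is 0.398 (normal) or 0.400 (t).
- 25% attrition: n = 120 × 0.75 = 90. The result is 0.418 (normal) or 0.420 (t).

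Both figures reproduce. They rest on an unadjusted test, so the covariate rule does not enter them.

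**2. How often the rule would add a covariate.** The article does not list the candidates. Table 3 marks 20 measures at baseline if the five cognitive tests are counted singly. WMFT time is already a fixed covariate and Fugl-Meyer presumably is too, which leaves 18; demographics come on top. Under correct randomization with k independent tests at 0.05, P(at least one flag) = 1 − 0.95^k.

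| k | Expected flags (0.05k) | Independent | Correlation 0.3 | 0.5 | 0.7 |
|---|---|---|---|---|---|
| 10 | 0.5 | 40% | – | – | – |
| 18 | 0.9 | 60% | – | – | – |
| 20 | 1.0 | 64% | 54% | 42% | 29% |
| 30 | 1.5 | 79% | 66% | 51% | 34% |

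The correlated columns assume one common correlation between the test statistics. Many of the instruments overlap in content, so those columns are more realistic than the independent one.

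**3. Whether the choice of groups matters.** Simulation with 120 per arm and no true differences compared a three-arm ANOVA with an ASAP–DEUCC t-test. Each flags 5.0% of variables, and 2.5% are flagged by both. They therefore disagree on (5.0 − 2.5) + (5.0 − 2.5) = 5.0% of variables. With 20 independent candidates, the chance of at least one disagreement is 1 − 0.95^20 = 64%. This holds only if the Baseline section means three arms, and correlation between candidates would change it.

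**4. Error rate and power.** Simulation used 100 per arm, 10 or 20 candidates jointly explaining 20% or 40% of outcome variance, and a true difference of 0 or 0.40. All of these except the 0.40 are assumptions.

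| Candidates, variance explained | Type I, test-selected | Power, unadjusted | Power, test-selected | Power, all candidates fixed |
|---|---|---|---|---|
| 10, 20% | 0.043 | 80.2% | 80.3% | 86.1% |
| 10, 40% | 0.043 | 80.6% | 81.9% | 94.5% |
| 20, 20% | 0.044 | 81.1% | 81.0% | 84.7% |
| 20, 40% | 0.041 | 81.4% | 81.9% | 93.6% |

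With candidates unrelated to outcome, type I error was 0.052. Selection by imbalance moves power by −0.1 to +1.3 percentage points against no adjustment for these variables, so it captures almost none of the precision they could offer.

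**The case against.** The strongest reply has four parts.

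- **Much of the primary analysis is already fixed.** This stands. The four a priori covariates include baseline WMFT time and motor impairment, which enter whether balanced or not. The t-test cannot be touched by the rule, and the sample size rests on that kind of test. A reader might infer that the whole covariate set, or the whole primary analysis, is data-driven; the text does not support that. The article does not say which of the two analyses is decisive, but it does commit to reporting the adjusted one.
- **The two sections do not contradict each other.** This also stands. The Analysis plan can be read as the general rule applied to the primary contrast, and a rank-sum test suits pairwise comparisons. What remains is an ambiguity to resolve.
- **No false-positive risk is shown.** Correct. A reader might infer an inflated type I error, but the simulations show a slightly conservative test when candidates are prognostic. One or two extra degrees of freedom among about 180 to 198 completers are negligible.
- **Candidate lists and thresholds belong in the analysis plan.** True, and their absence is not the point here. The selection rule itself is stated in the article, twice.

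**Conclusion.** The point holds for the additional covariates only. The article commits the adjusted primary and secondary models to variables picked by tests of baseline imbalance. Such tests carry no information on prognostic value, and the adjusted estimate, interval and p-value therefore depend on chance imbalance. A changed model is a realistic prospect: about 64% with 20 independent candidates, and roughly 30% to 54% with correlations of 0.7 to 0.3. These figures assume the number of candidates, a 0.05 threshold and the correlation. A higher figure, such as the 79% for 30 independent tests, should not be read as the plan's own, because the article neither lists 30 candidates nor suggests independence.

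The harm is a model not fixed in advance, with slightly miscalibrated error (about 0.041 to 0.044 with prognostic candidates). It is not a false-positive problem, and no sample-size figure is wrong. The change should be made before the final analysis.

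**What to change.** 1. In Baseline, delete the closing sentence and the stated aim of testing in order to decide on adjustment. Replace the tests with descriptive summaries by arm.
2. In Analysis plan, delete the clause that adds variables imbalanced between ASAP and DEUCC.
3. State that every comparison, including those with UCC, adjusts for site, initial motor impairment, stroke duration and the baseline value of the outcome being analysed.
4. Label any adjustment for observed imbalance as a sensitivity analysis, and say which arms are compared.

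**Cost.** This rewrites a few sentences rather than making two deletions. The article reports an interim analysis completed in November 2011 with enrolment still open, so it would be a documented plan change before the final analysis. In some scenarios a little precision is given up, at most 1.3 percentage points of power in the table above, and the sensitivity analysis would still show that adjusted result. The 85% to 95% power of a model containing all prognostic variables is not a gain from this fix, which keeps only the pre-named set. The total of 360 and the detectable differences of 0.40 and 0.42 are unchanged.
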